### 3. Background

Kidney transplant recipients are at high risk for a severe COVID-19 disease course and therefore prioritized to receive early vaccination against SARS-CoV-2 (1, 2). In general, the immune response to vaccination is reduced in immunosuppressed individuals including kidney transplant recipients. A recent study from Israel confirmed that only 37.5% of kidney transplant recipients developed detectable antibodies against the spike protein following full vaccination with BNT162b2 (Pfizer-BioNTech) (3). The type of maintenance immunosuppression may have a significant impact on the immune response in kidney transplant recipients. Patients treated with co-stimulation blockade (Belatacept) as maintenance immunosuppression showed even lower immunization rates of only 5.7 % (4).

Several strategies have been proposed to improve response to SARS-CoV-2 vaccination including additional dosing and mixing different vaccine types to broaden the presented antigen repertoire (heterologous vaccination or “mix-and-match strategy”) (5). Recent data show a higher reactogenicity of heterologous boosting in the general population (6). In the European Union there are currently two different classes of SARS-CoV-2 vaccines available: a) mRNA (mRNA-1273 [Moderna Biotech] and BNT162b2 [Pfizer-BioNTech]) and b) viral vector-based vaccines (ChAdOx1 [AstraZeneca] and Ad26COVS1 [Jansen]). Of these Ad26COVS1 is the only vaccine that has been shown to induce a protective immune response after a single dose (7). Kidney transplant recipients in Austria have primarily been vaccinated with mRNA-based vaccines.

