### Randomization

Randomization will be performed as soon as the SARS-CoV-2 antibody status is available.

- Patients included in the study will be randomized 1:1 to receive a third dose of the previously administered mRNA vaccine (mRNA-1273 or BNT162b2) or a single dose of Ad26COVS1
- Randomization will be stratified by the maintenance immunosuppressive regimen calcineurin inhibitor (CNI) vs co-stimulation blockade (Beletaccept)
- To ensure that comparison groups will be of approximately the same size a block randomization will be used in order to balance subjects randomized to each group (<https://www.meduniwien.ac.at/randomizer/>).

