## 8. Statistical analysis

### Sample size calculation

For testing the primary study endpoint (positive antibody to the SARS-CoV-2 vaccine) we assume a response rate of 30% and 50% in the mRNA and the viral vector-based vaccine treatment arms and expect a dropout rate of a maximum of 5%. Currently, no data on a third vaccination in kidney transplant recipients exist. The 30% response rate for the homologous vaccination group has been chosen expecting a slightly lower response rate to the third vaccination in kidney transplant recipients who did not respond to the standard 2-dose vaccination regime compared to the initial response rate of kidney transplant recipients to

the standard 2-dose vaccination regime (37% response rate). The 50% response rate estimate for the heterologous vaccination groups is based on early data from studies investigating heterologous vaccination which showed a higher reactogenicity after the heterologous vaccination. Enrollment of 100 patients per group will provide 80% power (alpha-error: 5%) to detect a difference in response between the two treatment groups.

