### Endpoint analysis

For all endpoints a per protocol analysis will be carried out.

For the primary endpoint (positive humoral immune response to SARS-CoV-2 vaccination at 4 weeks after the vaccination) SARS-CoV-2 S IgG antibody test results will be recorded and counts and percentages of patients exceeding the manufacturer defined cutoff of 0.8U/ml in each treatment arm will be reported. A chi-squared test will be employed to test for statistically significant differences in the number of responders (antibody concentration exceeds the manufacturer defined cutoff of 0.8U/ml) between the treatment arms.

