Before carrying out any endpoint analysis the number of study participants either on co-stimulation blockade or CNl as well as the number of patients who were initially vaccinated with either mRNA-1273 or BNT162b2 will be determined. In case of sufficient number of study subjects with different immunosuppressants or initially received vaccines the statistically analysis plan will be updated to introduce additional stratification.

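### The primary chi-squared test ignores the CNI/belatacept stratum used at randomisation; a stratified test is a free improvement, and the sample size is not wrong

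*Protocol*

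**What the plan says.** - **Protocol section 6, Randomization:** "Randomization will be stratified by the maintenance immunosuppressive regimen calcineurin inhibitor (CNI) vs co-stimulation blockade (Beletaccept"). Allocation is 1:1 in blocks.
- **Section 8, Endpoint analysis:** for the primary endpoint at week 4, "A chi-squared test will be employed to test for statistically significant differences in the number of responders" between the arms. No stratum enters. The responder endpoints at weeks 8, 12, 24 and 48 are analysed the same way.
- **Section 8, last paragraph of Secondary endpoint analysis:** patients are to be counted by immunosuppressant and by initial mRNA vaccine before any endpoint is analysed. Then: "In case of sufficient number of study subjects with different immunosuppressants or initially received vaccines the statistically analysis plan will be updated" so as to add stratification.
- **Section 3, Background:** 37.5% of kidney transplant recipients had antibodies after two doses in one study; in another, patients on belatacept "showed even lower immunization rates of only 5.7 % (4").
- **Section 8, Sample size calculation:** "we assume a response rate of 30% and 50% in the mRNA and the viral vector-based vaccine treatment arms", with dropout of at most 5% and 100 patients per group for 80% power at a 5% alpha.
- **Section 5, Study design:** only the patient is blinded.

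**The concern.** Stratified randomisation removes most of the chance imbalance in the stratum between the arms. A plain chi-squared test does not use this. Its variance still includes the difference in response between CNI and belatacept patients, although the design keeps that difference from adding noise to the treatment comparison. If the stratum is prognostic, the test rejects less often than it could: true size falls below 5%, and some of the power that the design makes available is not collected.

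The conditional paragraph adds a second issue. It refers to any endpoint analysis, so it covers the primary endpoint. It does not say what number is enough, which of the two factors would enter, which stratified method would be used, or whether the update would replace the primary chi-squared test. Four primary tests therefore remain possible: unstratified, by immunosuppressant, by initial vaccine, or by both. A threshold and a method might be left to a separate analysis plan. Whether the named primary test stands is something the protocol itself should settle.

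**Working it through.** **1. Reproduce the plan's figure.** Inputs from Sample size calculation: p1 = 0.30, p2 = 0.50, alpha 5%, power 80%. Sidedness is not stated; two-sided is assumed.

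n per arm = [1.96·√(2·p̄·q̄) + 0.8416·√(p1q1 + p2q2)]² / (p2 − p1)², with p̄ = 0.40

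= [1.96·√0.48 + 0.8416·√0.46]² / 0.04 = (1.358 + 0.571)² / 0.04 = 93.

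With 5% dropout, 93/0.95 = 98, against 100 planned. Power by the same formula is 80.8% with 95 evaluable per arm and 82.8% with 100. The stated 80% is reproduced for the unstratified test without continuity correction.

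**2. Why the plain test is conservative.** Suppose both arms share an overall rate of 30%, a proportion s are on belatacept with response 5.7% (the background figure, used here as an assumption), and strata are balanced between arms. The chi-squared test uses V = 0.30 × 0.70 = 0.21. The variance that applies is the within-stratum part:

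W = (1 − s)·p_C(1 − p_C) + s·0.057·0.943, where p_C = (0.30 − 0.057s)/(1 − s).

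True size is approximately 2[1 − Φ(1.96/√(W/V))].

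- s = 5%: p_C = 0.313, W = 0.207, W/V = 0.985, critical value 1.975, size about 4.8%.
- s = 30%: p_C = 0.404, W = 0.185, W/V = 0.879, critical value 2.09, size about 3.7%.

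Simulation agrees. The plain test's size is about 4.9%, 4.7%, 4.3% and 3.7 to 3.8% at shares of 5%, 10%, 20% and 30%. CMH stays at 4.9 to 5.0%. A higher common response rate makes the plain test more conservative: at 40% its size is about 3.5% and 2.7% at shares of 20% and 30%.

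**3. Power.** The CMH statistic is [Σ(a_k − n_1k·m_k/N_k)]² / Σ[n_1k·n_2k·m_k(N_k − m_k) / (N_k²(N_k − 1))], summed over the two strata. Here a_k is the responders in one arm, n_1k and n_2k the arm sizes, m_k all responders and N_k all patients in stratum k. The simulation used 95 per arm, balanced strata, overall rates held at 30% and 50%, and assumed belatacept response of 5% and 10%.

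| Belatacept share (assumed) | Chi-squared | CMH | Gain (points) |
|---|---|---|---|
| 5% | 80.9% | 81.3% | 0.4 |
| 10% | 81.2% | 83.3% | 2.1 |
| 20% | 82.1% | 85.3% | 3.2 |
| 30% | 83.0% | 88.5% | 5.5 |

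**4. Sensitivity.** With belatacept response at 5.7% on mRNA and 5.7% to 25% on vector, the gain at 95 per arm runs from 0.1 to 6 points over the same shares. With 100 evaluable per arm it is smaller: under 0.1 points at a 5% share, 0.1 to 0.3 at 10%, 1.2 to 3.1 at 20% and 2.7 to 4.3 at 30%. At low shares, part of the gain at 95 per arm therefore reflects the discreteness of the tests.

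**5. The open choice of test.** As a worst case, suppose the most favourable of the four tests were always reported. Under the null, with 95 per arm, 15% on belatacept and 30% with the second mRNA vaccine, simulation gives rejection in about 5.3% to 5.6% of trials, depending on the response rates assumed. CMH by immunosuppressant alone gives 5.0% to 5.1%. The excess is about half a point at most.

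**The case against.** The strongest defence is that the named test is valid. It never exceeds 5%, it meets its 80% target in every scenario tried, and the power forgone lies above that target. This stands.

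The size of the gain depends on a belatacept share that the protocol does not give; at 5% the gain is negligible. The prognostic contrast is also borrowed. The 37.5% and 5.7% come from separate two-dose studies, whereas this trial enrols patients without antibodies after two doses, so the contrast after a third dose is unknown. Nor does the protocol give a reason for stratifying; the background says only that the regimen may matter. All of this stands and limits what can be said about magnitude.

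A reader might infer that the team could choose the primary test after seeing results, since only the patient is blinded. The text does not support that reading as stated: the trigger is a count of two baseline factors, made before any endpoint is analysed. What remains is narrower. Nothing requires the decision to come before antibody results exist, what counts as enough is a judgement, and those making it are not stated to be blinded.

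**Conclusion.** The mismatch is real and worth correcting as a free improvement. The stratified design is paired with an unstratified primary test, which is valid but conservative if the stratum is prognostic. At 95 per arm, CMH adds about 0.4 to 5.5 points of power as the belatacept share rises from 5% to 30%. This rests on assumed shares, assumed belatacept response and balanced strata. The case for a fixed primary test does not depend on the share, but the harm from leaving it open is small, at about half a point of type I error even under deliberate selection.

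Two stronger readings should be resisted. The sample size is not wrong: the stated power is reproduced and holds for the planned test. Nor is the type I error of the planned test inflated: the departure is in the conservative direction.

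**What to change.** In section 8, Endpoint analysis:

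- Make the primary test a CMH test stratified by CNI versus belatacept, reported with a stratified risk difference and 95% confidence interval.
- Use the same test for the responder endpoints at weeks 8, 12, 24 and 48.
- Keep the unstratified chi-squared test as a sensitivity analysis.

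At the end of section 8, delete the conditional update, or restrict it to supportive analyses and state that the primary test does not change. No minimum stratum count is needed for the CMH test, because a sparse stratum simply contributes little to the statistic.

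The cost is wording only. The stratum is needed to randomise each patient, so no further data or patients are required and the sample size can stay as it is.

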### Secondary endpoint analysis

All secondary endpoint analysis will be conducted in an exploratory fashion and no adjustment for multiple testing will be performed.

- Number of patients presenting a positive humoral immune response at 8, 12, 24 and 48 weeks after vaccination will be analyzed in the same fashion as the primary endpoint.
- For the analysis of number of detectable antibodies at 4, 8, 12, 24 and 48 weeks after vaccination ELISA readouts (U/ml) will be recorded. At each time point their median and interquartile range in each treatment arm will be determined and a t-test will be

performed to determine if there is a statistically significant difference between the means of the logarithmized ELISA readouts (U/ml) of the two treatment arms.

- For the analysis of number of patients presenting a positive cellular immune response to SARS-CoV-2 vaccination at 4 weeks after the vaccination the extracellular IFN $\gamma$  concentration in a negative control sample and after ex-vivo re-stimulation with a SARS-CoV-2 spike protein peptide pool will be recorded for all patients. Doubling of IFN $\gamma$  concentration after re-stimulation will be considered as positive cellular response to the vaccination. Counts and percentages of patients with positive response will be reported for each treatment arm. A chi-squared test will be employed to test for statistically significant differences in the number of responders between the two treatment arms.
- For the analysis of the strength of the cellular immune response at 4 weeks after vaccination the extracellular IFN $\gamma$  concentration in negative control sample and after ex-vivo re-stimulation with a SARS-CoV-2 spike protein peptide pool will be recorded for all patients. IFN $\gamma$  concentration from the patient specific negative control samples will be subtracted from the re-stimulated samples to normalize for patient specific differences in cellular activation. Median and interquartile range of the normalized IFN $\gamma$  concentrations after re-stimulation will be calculated for both treatment arms and a t-test will be performed to determine if there is a statistically significant difference between the two treatment arms with respect to the means of the logarithmized IFN $\gamma$  concentration after re-stimulation.
- For the analysis of SARS-CoV-2 infection after a third vaccination, counts and percentages of individuals with SARS-CoV-2 infection by weeks 24 and 48 will be determined

Before carrying out any endpoint analysis the number of study participants either on co-stimulation blockade or CNl as well as the number of patients who were initially vaccinated with either mRNA-1273 or BNT162b2 will be determined. In case of sufficient number of study subjects with different immunosuppressants or initially received vaccines the statistically analysis plan will be updated to introduce additional stratification.

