### Inclusion criteria

- patient has received a kidney transplantation
- full SARS-CoV-2 vaccination with mRNA vaccine (two doses) at least 4 weeks before screening
- > 18 years of age
- no SARS-CoV-2 spike protein antibodies at least 4 weeks after the second dose of an mRNA vaccine

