### Laboratory testing

- SARS-CoV-2 spike protein and nucleocapsid antibodies at Visit 1, Visit 3, Visit 4, Visit 5, Visit 6 and Visit 7 (9ml blood)
- SARS-CoV-2 specific T- cell response at Visit 1 and Visit 3 (3x8 ml blood)

Antibodies will be measured by the Department of Laboratory Medicine using clinically validated ELISA tests (Roche, Switzerland). SARS-CoV-2 specific T-cell responses will be assessed by QuantiFERON assays with SARS-CoV-2 specific peptides at the research laboratory of the Division of Nephrology (Quiagen, Netherlands).

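### Both cellular endpoints use the week 4 sample alone, although the visit 1 T-cell result is available and would separate new responses from those left by doses 1 and 2

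*Protocol*

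**What the plan says.** - **When T cells are measured.** Protocol section 6, Laboratory testing, lists "SARS-CoV-2 specific T- cell response at Visit 1 and Visit 3 (3x8 ml blood"; Table 1 shows the same schedule.
- **Who enters.** Section 5, Inclusion criteria, requires "full SARS-CoV-2 vaccination with mRNA vaccine (two doses) at least 4 weeks before screening" and "no SARS-CoV-2 spike protein antibodies at least 4 weeks after the second dose of an mRNA vaccine". Neither the inclusion nor the exclusion criteria mention T-cell status.
- **Responder rule.** Section 8, Secondary endpoint analysis, records IFN-gamma in a negative control and after peptide stimulation. A doubled "concentration after re-stimulation will be considered as positive cellular response to the vaccination". The test is fixed: "A chi-squared test will be employed to test for statistically significant differences in the number of responders between the two treatment arms".
- **Strength.** In the same section, "concentration from the patient specific negative control samples will be subtracted from the re-stimulated samples", and the arms are compared by a t-test on a log scale.
- **Visit 1 value.** Neither analysis mentions it. The paragraph that closes section 8 foresees extra stratification only by immunosuppressant and by initial vaccine.
- **Status.** "All secondary endpoint analysis will be conducted in an exploratory fashion and no adjustment for multiple testing will be performed".

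**The concern.** The negative control removes IFN-gamma release that is not specific to spike. It cannot remove spike-specific T cells left by doses 1 and 2. The week 4 rule therefore shows that spike-reactive T cells are present, not that the study dose induced them, yet the result is named a response to the vaccination.

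The primary endpoint avoids this because antibody negativity is an entry criterion, so a positive antibody result at week 4 is new. The cellular endpoints lack that safeguard, and the visit 1 assay could supply it. At stake are how the published per-arm percentages are read, and the precision of both cellular comparisons.

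**Working it through.** **Inputs.** From Sample size calculation: "we assume a response rate of 30% and 50% in the mRNA and the viral vector-based vaccine treatment arms", 100 per group, 80% power, 5% alpha (sidedness not stated; two-sided used here) and at most 5% dropout. These figures concern the antibody endpoint; the protocol gives none for the cellular endpoints. Assumed: the baseline-positive share b, its persistence to week 4, and the visit 1 to week 4 correlation r.

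**1. The plan's own figure.** n = [1.96·√(2·0.40·0.60) + 0.842·√(0.30·0.70 + 0.50·0.50)]² / 0.20² = 93 per arm, and 93/0.95 = 98. The stated 100 reproduces and is not in question. With 100·0.95 = 95 evaluable per arm, power is 81%.

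**2. Dilution of the responder endpoint.** If a share b of each arm is already positive and stays positive, the observed rate is b + (1 − b)·p. The difference becomes (1 − b)·20 points. Visit 1-negative patients number 95·(1 − b) per arm and keep the full 20 points. Power below is exact for the Pearson chi-squared test; the normal approximation agrees to about one point.

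| b | Observed rates | Difference | Power, rule as written | Visit 1-negative per arm | Power in these |
|---|---|---|---|---|---|
| 0 | 30% vs 50% | 20 points | 81% | 95 | 81% |
| 5% | 33.5% vs 52.5% | 19 points | 75% | 90 | 79% |
| 10% | 37% vs 55% | 18 points | 70% | 86 | 77% |
| 20% | 44% vs 60% | 16 points | 60% | 76 | 73% |
| 30% | 51% vs 65% | 14 points | 49% | 66 | 65% |

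At b = 20%, 20 of the 44 points reported for the mRNA arm would have been there before the study dose.

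**3. What stratifying by visit 1 status recovers.** In a Cochran-Mantel-Haenszel test, a stratum in which everyone responds adds nothing to the numerator or the variance, so the test draws only on the visit 1-negative stratum. Take b = 20%, with 19 positive and 76 negative patients per arm. The expected excess of responders in the vector arm is 76·(0.50 − 0.40) = 7.6. With equal arms, the null variance is N²·p(1 − p)/[4(N − 1)].
- Unstratified: 190²·0.52·0.48/(4·189) = 11.92, so expected z = 7.6/√11.92 = 2.20.
- Stratified, all positives persist: 152²·0.40·0.60/(4·151) = 9.18, so z = 2.51.
- Stratified, 80% persist in both arms: the positive stratum adds 38²·0.80·0.20/(4·37) = 1.56, so z = 7.6/√10.74 = 2.32. The unstratified z stays at 2.20, because the pooled rate is then 0.48.

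The gain is therefore largest when persistence is complete and smaller otherwise.

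**4. Strength.** Adjusting for the visit 1 value multiplies residual variance by 1 − r². At r = 0.3, 0.5 and 0.7 the factor is 0.91, 0.75 and 0.51, a reduction of 9%, 25% and 49%. At r = 0.5 this equals 1/0.75 = 1.33 times the patients.

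**The case against.** Four objections have weight.

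- **Exploratory endpoints.** No power is claimed for either cellular endpoint, so the figures above are not a shortfall against a promise. This stands; they only show what using the visit 1 value could gain.
- **Valid comparison.** A reader might infer that the arm comparison is biased, or that the primary result is at risk. The documents support neither. Allocation is 1:1 and randomised, so baseline positives fall equally in both arms on average, and the antibody endpoint has its own entry criterion. T-cell positivity at week 4 under each strategy is also a legitimate question. What remains is the label, the per-arm rates and the efficiency.
- **Unknown b.** A reader might also take dilution as established. The documents do not give b, the Background describes reduced immune responses in these patients, and at b = 0 the problem vanishes. The recoverable part is also less than the total loss: 13 points at b = 20% (60% to 73%), not the full 21 (81% to 60%).
- **Left to the analysis plan.** Covariate adjustment often is, and a plan that is not shown may add it, so one cannot say that the visit 1 data are discarded. But the protocol itself fixes the responder rule and both unadjusted tests. For strength, the t-test is valid, and ANCOVA is a gain in efficiency rather than the correction of an error.

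The choice of remedy also matters. Restricting the main analysis to visit 1-negative patients changes the question and drops any boosting in the others. Logistic regression on visit 1 status has no finite estimate for that term if all baseline positives stay positive.

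**Conclusion.** The point holds as a free improvement to two exploratory secondary endpoints. As written, a patient who is T-cell positive before the study dose counts as responding to it. This overstates per-arm response rates and, where such patients exist, shrinks the arm difference by the factor 1 − b.

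Under the stated assumptions, using visit 1 status raises power by about 4 points at b = 5%, 7 at 10%, 13 at 20% and 16 at 30%. It raises it by nothing at b = 0, and by less if baseline positives do not all persist. The reading of the text is certain. The size is not, because b, persistence and r are all assumed, and the 30% and 50% are borrowed from the antibody endpoint.

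**What to change.** In section 8, Secondary endpoint analysis, with matching wording under Secondary endpoints in section 4:

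- Keep all patients in the cellular responder analysis and compare arms with a Cochran-Mantel-Haenszel test stratified by visit 1 T-cell status, judged by the same doubling rule. This test tolerates a stratum with 100% response.
- Report visit 1 positivity by arm.
- Report new response among visit 1-negative patients as a supporting result, and keep the term response to the vaccination for that result.
- Analyse strength by ANCOVA on ranked or suitably transformed IFN-gamma, with the visit 1 background-subtracted value and the randomisation stratum as covariates. The transformation must cope with zero or negative values after subtraction.

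Fix this before week 4 results are compared by arm, so that the choice cannot depend on them. The cost is wording only: the visit 1 assay is already scheduled for every patient, and no extra visit, blood or assay is needed.

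### Cellular-strength endpoint: the plan subtracts background and then t-tests a logarithm, so the test is either undefined for some patients or made on a quantity other than the one summarised

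*Protocol*

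**What the plan says.** The rule stands in one bullet of the protocol, section 8, Secondary endpoint analysis, and has three steps.

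1. Normalise: IFN-gamma from the "patient specific negative control samples will be subtracted from the re-stimulated samples to normalize for patient specific differences in cellular activation".
2. Summarise: "Median and interquartile range of the normalized IFN"-gamma concentration are reported for each arm.
3. Test: a t-test is to show whether "there is a statistically significant difference between the two treatment arms with respect to the means of the logarithmized" IFN-gamma concentration after re-stimulation.

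Step 3 does not repeat that the value is normalised. The endpoint list in section 4 defines strength as the IFN-gamma concentration after re-stimulation and mentions no subtraction. No offset, floor or alternative test is given for differences at or below zero.

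The preceding bullet defines the cellular responder on a ratio scale: a doubling of IFN-gamma over the negative control "after re-stimulation will be considered as positive cellular response to the vaccination". The section declares all secondary analyses exploratory, without adjustment for multiple testing.

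**The concern.** Subtraction and logarithm do not combine when the background-corrected value can be zero or negative. Without a T-cell response, the stimulated and control readings differ mainly by noise, so some differences fall at or below zero.

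The bullet fixes the subtraction, the transformation and the test, but not what happens to those patients. Statistical software would usually return missing values and drop them silently. The comparison would then cover only patients whose re-stimulated value exceeded control. That condition is part of the outcome and arises after randomisation, and the share removed is larger in the arm with fewer responders.

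Logging the raw re-stimulated value avoids the undefined logarithm. It also leaves in the test the between-patient activation that the bullet says is to be removed, and the p-value then belongs to a different quantity from the median printed beside it.

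**Working it through.** **Inputs.** The protocol gives no figure for IFN-gamma, so there is no stated result to reproduce for this endpoint. From the sample size section I take only 100 per arm and 5% dropout, hence 100 x 0.95 = 95 evaluable. (That calculation is sound: 30% against 50%, two-sided 5%, 80% power needs 93 per arm, and 93/0.95 rounds up to 98, within the stated 100.) All IFN-gamma distributions below are assumptions. The 30% and 50% cellular response rates are borrowed from the antibody assumption.

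**Step 1: when is the log undefined?** Let S be the re-stimulated reading and C the control. log(S - C) exists only if S/C > 1. A responder has S/C of at least 2. A non-responder with S/C between 1 and 2 therefore still has a valid logarithm.

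**Step 2: how often, in patients without a response?** Take log(S/C) as normal with mean ln R and SD s. Then P(S <= C) = Phi(-ln R / s). For example, R = 1.25 and s = 0.4 give Phi(-0.223/0.4) = 28.8%.

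| Typical ratio R | s = 0.2 | s = 0.4 | s = 0.7 |
|---|---|---|---|
| 1.0 | 50% | 50% | 50% |
| 1.1 | 31.7% | 40.6% | 44.6% |
| 1.25 | 13.2% | 28.8% | 37.5% |
| 1.5 | 2.1% | 15.5% | 28.1% |

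Restricting to patients with an observed ratio below 2 raises the shares somewhat, at most to 0.5/0.839 = 59.6% (R = 1.0, s = 0.7).

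**Step 3: imbalance between arms.** With R = 1.0 and 30% against 50% responders, the undefined share is about 0.5 x 70% = 35% in the mRNA arm and 0.5 x 50% = 25% in the vector arm. About 95 x 0.65 = 62 and 95 x 0.75 = 71 patients remain.

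**Step 4: effect on the test.** I simulated 4,000 trials with 95 per arm. Control readings were lognormal (median 0.05, log SD 0.6). The log ratio had mean ln 6 and SD 0.8 in responders, and mean 0 and SD 0.3 in the others. Undefined logs occurred in 35% and 26% of patients.

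| Rule | Trials significant at 5% |
|---|---|
| log(S - C), undefined dropped | 47% |
| log S, unsubtracted | 55% |
| log(S - C), floor 0.001 | 66% |
| log(S - C), floor 0.01 | 68% |
| log(S/C) | 66% |
| Rank test on S - C, all patients | 63% |

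Over a wider set of assumed distributions, 13-36% of the mRNA arm and 9-27% of the vector arm were undefined. Power was 32-59% with undefined logs dropped, 33-54% for the raw log and 47-64% for the rank test. Type I error stayed near 5% throughout. Where almost all differences are positive, the gap between dropping and ranking closes.

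**The case against.** **The raw value may be what is meant.** The test clause omits the word for normalised, and section 4 defines the endpoint without subtraction. On that reading the test can be computed. This stands as a possible reading, so the text cannot be said to prescribe an undefined logarithm outright. It does not clear the bullet, because the test then ignores the normalisation set out just before it and is not a test of the summarised quantity.

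**The share may be small.** A reader might infer that half of all non-responders have no logarithm. The documents do not support that as fact. It needs a ratio centred on 1, and the table falls to 2.1% under other assumptions.

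**The loss is moderate.** A reader might also infer that dropping removes most of any treatment effect. It does not. In step 3, responders form 30/65 = 46% and 50/75 = 67% of the kept patients, a gap of 20.5 points against 20 in all patients. Power falls largely through lost numbers, and false positives are not inflated. What remains is that the comparison is no longer between the groups as randomised.

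**Antibody levels.** It is tempting to extend the point to the t-test on the "difference between the means of the logarithmized ELISA readouts (U/ml) of the two treatment arms". Patients enter with "no SARS-CoV-2 spike protein antibodies at least 4 weeks after the second dose of an mRNA vaccine", and "we assume a response rate of 30% and 50% in the mRNA and the viral vector-based vaccine treatment arms", so 70% and 50% are expected not to exceed 0.8 U/ml. But 0.8 U/ml is a positivity cutoff, not a detection limit, and positive readouts below it can be logged. Coding of readouts below an assay limit is commonly left to the SAP, which is not at hand. At most, it is worth noting that the mean log is sensitive to that coding.

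**Conclusion.** The point holds for the cellular-strength endpoint. On the natural reading (normalise, log, test), the t-test is undefined for any patient with re-stimulated IFN-gamma at or below control. On the other reading, it tests something other than what is normalised and summarised. Either way the bullet needs a change. This is not a detail left to the SAP, since the protocol itself names the subtraction, the logarithm and the test.

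The size rests wholly on assumed distributions. In the worked example, the unfixed choice moves power from 47% to 68%. The rank test is not the most powerful option in that example; its merit is that it keeps every analysed patient and needs no floor.

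Severity is low to moderate. The endpoint is exploratory. The primary chi-squared test, the sample size and the cellular responder analysis, which uses a ratio and no logarithm, are unaffected. The antibody t-test is not part of the finding.

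**What to change.** In the cellular-strength bullet of section 8, state which IFN-gamma quantity is tested, and use the same quantity for summary and test. There are two sound options.

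- **Rank test.** Replace the log t-test by a Wilcoxon rank-sum test on the background-subtracted value for all analysed patients, negative values included. It may be stratified by the randomisation factor (calcineurin inhibitor or co-stimulation blockade). The planned median and interquartile range then describe the tested quantity.
- **Log ratio.** Keep a t-test, but on log(re-stimulated/control), and summarise that ratio. This normalises each patient to the own control and matches the doubling criterion. It needs both readings above zero, so a rule for zero readings must be given with it.

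Align the endpoint definition in section 4 with the choice, and fix it before the data are seen.

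The cost is wording only; both readings are already recorded for every patient. The downside of the rank test is a less familiar effect measure than a ratio of means. As an optional addition, state how antibody readouts below the assay limit are coded.
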